## Abstract

Most human *Plasmodium* infections in western Kenya are asymptomatic and are believed to contribute importantly to malaria transmission. Elimination of asymptomatic infections requires active treatment approaches, such as mass testing and treatment (MTaT) or mass drug administration (MDA), as infected persons do not seek care for their infection. Evaluations of community-based approaches that are designed to reduce malaria transmission require careful attention to study design to ensure that important effects can be measured accurately. This manuscript describes the study design and methodology of a cluster-randomized controlled trial to evaluate a MTaT approach for malaria transmission reduction in an area of high malaria transmission. Ten health facilities in western Kenya were purposively selected for inclusion. The communities within 3 km of each health facility were divided into three clusters of approximately equal population size. Two clusters around each health facility were randomly assigned to the control arm, and one to the intervention arm. Three times per year for 2 years, after the long and short rains, and again before the long rains, teams of community health volunteers visited every household within the intervention arm, tested all consenting individuals with malaria rapid diagnostic tests, and treated all positive individuals with an effective anti-malarial. The effect of mass testing and treatment on malaria transmission was measured through population-based longitudinal cohorts, outpatient visits for clinical malaria, periodic population-based cross-sectional surveys, and entomological indices.

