## Methods

### Study objectives

The objective of this study was to measure changes in malaria transmission outcomes resulting from community MTaT compared to case management alone in a setting of high coverage with LLINs. Specific primary objectives were to evaluate the:Incidence of *Plasmodium falciparum* infection and clinical malaria.Prevalence of *P. falciparum* infection and anaemia.Sporozoite and oocyst rates in malaria vectors.

Secondary objectives included measuring the acceptability of MTaT to the local community, assessing adherence to anti-malarial regimens, costing of the intervention, and documenting the impact of MTaT on gametocyte prevalence and serologic markers of transmission.

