### Study design

The study was designed as a three-arm cluster-randomized controlled trial. Blinding of study participants or study staff to the intervention was not considered feasible or ethical. Ten of the 61 health facilities within the HDSS in Siaya County were purposively selected based on the following criteria: (1) high absolute malaria caseloads, (2) proximity of the facility to major roads for transport of supplies and samples, (3) government owned and run, and (4) minimum overlap with other known interventional/observational studies in the facility catchment; health facilities were chosen to maximize the distance between them, and all were at least 5 km from the next nearest health facility. All villages whose midpoint was located within 3 km of each health facility were included in the study. The villages surrounding each health facility were divided into three clusters along village boundaries such that the population was approximately evenly divided. One of the three clusters surrounding each health facility was randomly selected for the intervention, and the remaining two served as controls (Fig. 1). The purpose of the second control cluster was to allow the possible addition of a second intervention in the future. As no additional intervention arm was included in the study, for analysis purposes, the two control clusters were merged so that the study comprised 10 intervention and 10 control clusters with equal sample sizes. To reduce contamination between intervention and control clusters, the sampling frame for evaluations were limited to a core area within each cluster. The core area was defined as an area within the cluster that was ≥300 m from the perimeter of the cluster. The 300 m distance was chosen on the basis of previous studies at the site that indirectly demonstrated that the mass effect of a community based intervention (LLINs) extended to approximately 300 m based upon both entomologic [40] and epidemiologic [41] data. The area between the core and the perimeter of the cluster was defined as the buffer; though the intervention was performed in the buffer, data from individuals residing within the buffer area were not used for evaluations.

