#### Mass testing and treatment rounds

A mathematical model was calibrated to a pre-trial prevalence of 35% by slide microscopy between 2 and 10 year olds, incorporating historical trends in insecticide-treated net use and first-line treatment, as well as vector species composition and bionomics informed by entomology data from the KEMRI and CDC study site. The double-peaked seasonality pattern was generated using local rainfall data. All possible monthly combinations of a 2 year, three round per-year MTaT providing a curative drug with a prophylactic period fitted to pharmacokinetic/pharmacodynamic data of the efficacy of dihydroartemisinin–piperaquine at 80% coverage, were simulated. Correlation between rounds were simulated with a co-efficient calibrated to mimic a hard-to-reach 10% of the population who only have a 10% probability of taking the drug at each round. The optimal combination was that which minimized clinical incidence within the population over the course of the intervention. Model results suggested that three annual rounds should be performed (1) prior to the short rains, (2) after the short malaria peak, and (3) just prior to the long rains, before the major malaria transmission season ([name], personal communication).

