During MTaT rounds, CHVs visited every compound within the intervention clusters. After obtaining individual informed consent from all eligible members the CHV collected a blood sample using finger or heel prick to determine malaria parasitaemia by RDT (Carestart™ Malaria HRP-2/pLDH (Pf/PAN) Combo Test RDT; Somerset, NJ, USA). Additional drops were spotted on Whatman 903 filter papers (GE Healthcare, Marlborough, MA, USA) from the first 5000 participants encountered during the MTaT rounds to be used for real-time reverse transcriptase polymerase chain reaction (rRT-PCR) detection of malaria parasites. CHVs completed a short questionnaire programmed on PDAs using Visual CE version 12 (SYWARE^®^ Inc., Cambridge, USA) or tablets using Open Data Kit version 2.0 [43], to evaluate recent presence of malaria-associated symptoms, malaria prevention methods (e.g. LLIN use), care-seeking, use of medications, and migration. RDT positive women of child-bearing age (13–49 years of age) who were not visibly pregnant, reported a last menstrual period ≥4 weeks before the visit, and did not report being pregnant, were privately offered a urine pregnancy test at home. Those who refused pregnancy testing were referred to the closest study health facility for treatment. All participants testing positive for malaria or anaemia were treated according to an algorithm consistent with the Kenya Ministry of Health National Malaria Treatment Guidelines [44] that was pre-programmed into the PDA or tablet (Fig. 2). Those with signs of severe malaria (including prostration, altered consciousness) [44] or anaemia were referred to study health facilities for further evaluations and treatment. Study staff directly observed the first dose of anti-malarial treatment, and revisited a sample of 200 compounds, selected by probability proportional to size, to evaluate each individual who had been treated with anti-malarials one week after treatment for anti-malarial adherence. Individuals were asked how many tablets they took, and blister packs were observed for remaining tablets.

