#### Incidence of malaria infection

The incidence of malaria infection was measured using active surveillance in a population-based cohort from the intervention and control clusters. At each cross-sectional survey, a sub-sample of individuals were recruited from both the control and intervention arms to measure the incidence of *P. falciparum* infection over time. From within the 20 compounds in each of the 20 clusters included in the cross-sectional survey, 33 individuals were randomly selected for a total sample size of 660 individuals (330 control and 330 intervention) aged ≥1 year. At the time of recruitment, all cohort participants were provided an LLIN and tested for malaria, and were treated with artemether–lumefantrine for malaria to clear subpatent infections. Cohort participants made scheduled monthly visits to the closest study health facility, and were encouraged to attend the health facility in case of illness. At both scheduled and sick visits, participants were administered a questionnaire on recent history of fever, health-seeking behaviour, LLIN use, and medication use in the month since the previous visit. Blood samples were obtained by finger pricks at each scheduled and sick visit for malaria testing by RDT and microscopy, and haemoglobin testing using a HemoCue^®^. A blood spot was also dried on a Whatman 903 filter paper for testing by rRT-PCR. Treatment decisions were made according to RDT and Hemocue^®^ results. All blood smears were read within 24 h of the visit, and participants whose blood smears were positive and discordant with the RDT result were contacted by study staff and treated.

Cohort participants not arriving for a scheduled visit were called and reminded to visit. Study staff made home visits to evaluate participants who were unreachable or who were unable to come to the clinic. Attempts to contact participants were ceased if they failed to present to three consecutive scheduled monthly visits, but they were not withdrawn from the cohort.

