### Data analysis

The primary outcome of incidence and prevalence analyses, in the cohort and cross-sectional studies, respectively, were microscopically confirmed *P. falciparum* parasitaemia. Arm-specific unadjusted prevalence ratios (PR) for parasitaemia and anaemia were calculated using data from the series of pre- and post-intervention cross-sectional surveys. These data were analyzed with a log-binomial model using generalized estimating equations to account for clustering. Pre- and post-intervention PRs between arms were evaluated using the same model. The incidence of clinical malaria, diagnostically confirmed by either RDT or microscopy, presenting to the MTaT study health facilities (passive surveillance) was calculated. Total case counts originating from each study arm at each health facility per month was divided by the total population of the study arm residing in the catchment area of the health facility according to the HDSS. The incidence of infection was determined from the cohort data. A Cox-Proportional Hazards model was used to compare time to infection between arms. Adjusted models were created to account for confounders including socioeconomic status, anti-malarial use, and LLIN use. Socioeconomic status (SES) was assessed using principal component analysis models of household assets [58]. Sporozoite and oocyst rates were compared by logistic regression using generalized estimating equations to account for correlated observations within the households. All analyses were performed using SAS statistical software version 9.3 (SAS Institute, Carey, NC).

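### The adjusted models condition on anti-malarial use, which MTaT itself delivers, so they do not estimate the total effect of MTaT

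*Protocol article*

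**What the plan says.** All places are in the protocol article.

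- **Data analysis.** Unadjusted prevalence ratios come from a log-binomial GEE model of the surveys. For the cohort, "A Cox-Proportional Hazards model was used to compare time to infection between arms". The article then adds: "Adjusted models were created to account for confounders including socioeconomic status, anti-malarial use, and LLIN use". It does not say when or from which record anti-malarial use is taken, whether drug given in MTaT rounds counts, or whether the adjusted or unadjusted Cox result leads.
- **Study objectives.** The aim is to "measure changes in malaria transmission outcomes resulting from community MTaT compared to case management alone".
- **Study design.** "One of the three clusters surrounding each health facility was randomly selected for the intervention, and the remaining two served as controls".
- **Abstract.** In the intervention arm, teams "tested all consenting individuals with malaria rapid diagnostic tests, and treated all positive individuals with an effective anti-malarial".
- **Mass testing and treatment rounds.** "Study staff directly observed the first dose of anti-malarial treatment". The model used to time the rounds has MTaT "providing a curative drug with a prophylactic period".
- **Incidence of malaria infection.** Whenever cohort members were seen, as planned or because of illness, the article reports: "participants were administered a questionnaire on recent history of fever, health-seeking behaviour, LLIN use, and medication use in the month since the previous visit". Treatment in the cohort follows the RDT result, and smear-positive participants with a discordant RDT are also contacted and treated.

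**The concern.** A confounder of a randomised comparison would have to influence which arm a cluster was in. Anti-malarial use during follow-up cannot do that, because it comes after allocation. Allocation changes it, since handing out anti-malarials is what MTaT does. That makes it a mediator. It is also partly a consequence of the outcome, because a positive test leads to treatment in both arms.

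The stated objective is a total effect. A model that holds own drug use constant compares recent users with recent users and non-users with non-users, and so reports a residual effect. Incidence of infection is a primary objective, and it is the main outcome of the cohort in Table 1. If an adjusted hazard ratio nearer to one stood beside an unadjusted benefit, and the covariate was called a confounder, a reader would wrongly conclude that imbalance had explained the benefit away.

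**Working it through.** **1. Role of the covariate.**
- Allocation is random by cluster (Study design), so later drug use is not a cause of arm.
- MTaT delivers an anti-malarial to positives (Abstract; Mass testing and treatment rounds), so arm changes drug use.
- The drug is modelled as curative with a prophylactic period, so drug use changes infection.
- In the cohort, medication use is asked about the month since the previous visit, and positives are treated, so infection also changes recorded use.

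The second and third lines make drug use a mediator. The last makes it a consequence of the outcome.

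**2. The plan's own cohort figure.** Inputs from Incidence of malaria infection: r0 = 1.6 per person-year; a 30% reduction, so r1 = 1.12; coefficient of variation k = 0.25; 33 people per cluster for 2 years, so y = 66 person-years with no loss; c = 10 clusters per arm; alpha 5%, taken as two-sided. With the unmatched cluster formula for rates,

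power = Φ( √[ (c − a)(r0 − r1)² / ( (r0 + r1)/y + k²(r0² + r1²) ) ] − 1.96 ), where a = 0 or 1 for the small-sample correction.

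The denominator is 2.72/66 + 0.0625 × 3.8144 = 0.0412 + 0.2384 = 0.2796, and (r0 − r1)² = 0.2304.
- a = 0: √(2.304/0.2796) = 2.871, power 81.9%.
- a = 1: √(2.0736/0.2796) = 2.723, power 77.7%.

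The stated 80% is reproduced closely and is not in dispute. It gives the scale for the next step.

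**3. What adjustment leaves.** Let s be the share of the log effect carried by a person's own recorded drug use. The documents do not give s. With no other bias, the adjusted rate ratio is 0.70^(1 − s). Power uses the formula above with a = 1 and treats the variance as unchanged by adjustment, so it is approximate.

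| s (assumed) | adjusted rate ratio | power |
|---|---|---|
| 0% | 0.700 | 78% |
| 25% | 0.765 | 54% |
| 50% | 0.837 | 29% |
| 75% | 0.915 | 10% |
| 100% | 1.00 | 2.5% |

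**4. Why part rather than all.** A small illustration with assumed inputs: an MTaT treatment in 0.25 × 0.80 × 0.35 = 7% of intervention person-months, 15% background use in both arms, and a 90% lower infection rate in a month with drug use.
- Use in controls is 15%; mean relative rate 0.85 + 0.15 × 0.1 = 0.865.
- Use in the MTaT arm is 1 − 0.93 × 0.85 = 20.95%; mean relative rate 0.7905 + 0.2095 × 0.1 = 0.811.
- Ratio through own drug use alone: 0.811/0.865 = 0.94 unadjusted, 1.00 adjusted.
- With an added community effect of 0.80: 0.938 × 0.80 = 0.75 unadjusted, 0.80 adjusted.
- With an added community effect of 0.70: 0.938 × 0.70 = 0.66 unadjusted, 0.70 adjusted.

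Adjustment strips out the drug-carried part and leaves the community part. Here the drug-carried share of the log effect is ln 0.938/ln 0.750 = 0.064/0.287 = 22% and ln 0.938/ln 0.657 = 0.064/0.421 = 15%, so s could lie below the 25% row.

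**5. Why the direction is not certain.** The illustration lets drug use affect infection but not the reverse. In the trial, untreated people in the MTaT arm are mostly test-negative or unreached, whereas untreated controls include undetected carriers. Comparing these two groups could push the adjusted ratio below the true one. Recent users also differ by arm: in controls they are largely people treated for illness, and in the MTaT arm they include asymptomatic positives. The net selection bias cannot be signed from the documents.

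**The case against.** The strongest reply is that the adjusted models are not named as the main analysis. Unadjusted prevalence ratios are specified for parasitaemia and anaemia, and the adjusted models are mentioned only after the Cox comparison. The source and timing of the covariate are not given either, so a fuller document might confine it to baseline or to drug obtained outside the study. The first part stands for the surveys: those unadjusted ratios are untouched. It does not settle the Cox analysis, where the article does not say which result leads. The second part is possible, but nothing in the article supports it, and the medication record it describes for the cohort is taken at follow-up visits. Restricting the covariate to background use would not fully repair it, because case management is the comparator and MTaT may itself change how often people fall ill and are treated.

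Three stronger readings are tempting but not supported.
- **That adjustment removes the whole effect.** This holds only if own drug use carries all of it. MTaT is meant to lower transmission in the community, and adjusting for a person's own drug use does not block that route.
- **That the bias always runs towards no effect.** Removing the mediated part does so, but selection on treatment can act either way.
- **That LLIN use is the same fault.** If taken at follow-up it is post-randomisation, but MTaT delivers no nets and cohort members in both arms were given one at recruitment. The concern is much weaker.

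**Conclusion.** The concern holds for the adjusted models. As written they condition on a variable that MTaT changes and that infection also changes, and they call it a confounder. The adjusted arm coefficient is therefore not the effect of MTaT versus case management alone.

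The size is unknown, because the share carried by own drug use is not in the documents. Under an assumed share of 25% to 75%, the design rate ratio of 0.70 becomes about 0.77 to 0.91, before any selection bias of either sign. This rests on reading anti-malarial use as use during follow-up, which is the only record of medication use that the article describes for the cohort. The unadjusted prevalence ratios are unaffected. The harm is greatest if the adjusted Cox result is taken as the main result for incidence of infection.

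**What to change.** - Drop post-randomisation anti-malarial use from every model that estimates the effect of MTaT.
- State that the unadjusted comparison leads, or one adjusted only for covariates that MTaT cannot affect, for both the surveys and the Cox analysis. Age, SES and cluster-level baseline prevalence from the pre-intervention survey are suitable. Baseline prevalence should be taken at cluster level: compounds are drawn from the latest roster at each annual survey and some cohort members join at the year 1 survey, so the article shows no pre-MTaT individual record for them.
- Report anti-malarial use by arm as a process measure.
- Label any model that includes it as exploratory mediation.

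The cost is one re-run with no new data collection. The small downside is that the adjusted model no longer accounts for background drug use.

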### Measurement of malaria transmission outcomes

Four separate strategies were used to evaluate outcomes related to malaria transmission: (1) annual population-based cross-sectional studies for malaria prevalence, (2) active surveillance for malaria infection utilizing a longitudinal cohort, (3) passive surveillance of laboratory-confirmed clinical malaria cases in study health facilities, and (4) entomological transmission indices. Eligible participants residing within a household located within the core area were included in the sampling frame for study evaluations and analyses. Inclusion criteria, sample sizes, and main malaria transmission outcomes for each of the evaluations can be found in Table 1.

**Table 1 Tab1:** Inclusion criteria, sample size, and main outcome by evaluation type

Evaluation type	Inclusion criteria	Sample size	Main outcome
Cross-sectional studies	≥1 month of age	857 per arm	Community malaria prevalence
Longitudinal cohort study	≥1 year of age, not pregnant at time of recruitment	330 per arm	Incidence of malaria infection
Passive surveillance	Living within the core area of a cluster	N/A	Incidence of clinical malaria
Entomological surveillance	Household in either a control or intervention cluster	120 control and 60 intervention households per month	Monthly *P. falciparum* oocyst and sporozoite rates, *Anopheles* parity rate

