#### Entomological transmission indices

Monitoring was conducted to assess the impact of MTaT on entomological indices of malaria transmission by comparing the proportion of *Anopheles* mosquitoes with *P. falciparum* sporozoite and oocyst infections, and the parity rate, by study arm.

Each month, a simple random sample of twelve and six houses were selected (without replacement) from each of the ten control and intervention clusters, respectively, for pyrethrum spray catches (PSCs). Briefly, white sheets were placed over the surface of the floor and furniture between 0600 and 1200 h, and two collectors (one inside and one outside the house) sprayed around the eaves with 0.025% pyrethrum emulsifiable concentrate with 0.1% piperonyl butoxide in kerosene. The collector inside the house then sprayed the roof and walls of the house, and the house was closed for 10–15 min. Dead mosquitoes were then collected and placed on moist filter paper inside of petri dishes and returned to the laboratory.

Live collections using Prokopack [46] aspirators were performed for one week each month in each study arm. During the live sampling week, collectors visited as many households as possible until 1200 h. To maximize the number of specimens collected, the live collection methodology did not use a random sample. In each house, collectors spent 15–20 min aspirating mosquitoes, and those collected from the same house were placed into a single cage.

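### The sporozoite and oocyst comparison allows for correlation within households only, although MTaT was allocated to clusters, so its standard errors leave out between-cluster variation

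*Protocol article*

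**What the plan says.** Study objectives (protocol article) lists "Sporozoite and oocyst rates in malaria vectors" among the specific primary objectives.

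Study design sets the unit of allocation: "One of the three clusters surrounding each health facility was randomly selected for the intervention, and the remaining two served as controls". The two control clusters at each facility were later merged, so that "the study comprised 10 intervention and 10 control clusters with equal sample sizes".

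Under Entomological transmission indices, the monthly spray catches use "a simple random sample of twelve and six houses were selected (without replacement) from each of the ten control and intervention clusters", respectively. Live collections by aspirator are a separate activity, without a random sample of houses.

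Data analysis gives the model: "Sporozoite and oocyst rates were compared by logistic regression using generalized estimating equations to account for correlated observations within the households". The household is the only level of correlation named. For the prevalence surveys the same paragraph says: "These data were analyzed with a log-binomial model using generalized estimating equations to account for clustering".

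On the sampling frame, Study design says that "the sampling frame for evaluations were limited to a core area within each cluster", while the entomology row of Table 1 gives its inclusion criterion as "Household in either a control or intervention cluster".

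**The concern.** In a cluster-randomised trial the comparison between arms carries variation at the level that was allocated. A GEE sandwich variance sums squared score contributions over its subjects and takes different subjects as independent. With the household as subject, two houses in the same cluster contribute as if unrelated, and the variation between clusters never enters the standard error. Confidence intervals are then too narrow and the test rejects too often.

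At stake is a claim that MTaT reduced infection in the vector, one of the trial's listed primary objectives. The trial's own planning does not treat clusters as alike: the cross-sectional sample size assumes a CV of 0.3 and the cohort sample size one of 0.25.

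**Working it through.** **Stated sample.** 12 houses × 10 = 120 control and 6 × 10 = 60 intervention houses per month. This matches Table 1. The article gives no power calculation for this endpoint.

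**Inputs from the article.** 10 intervention and 10 merged control clusters; 120 and 60 houses per month; k (between-cluster CV) = 0.25 from the cohort sample size and 0.3 from the cross-sectional sample size. Both CVs are borrowed from human endpoints.

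**Assumptions.** 24 months of catches (the intervention ran for 2 years); sporozoite rate p = 3%; one tested mosquito per house; nominal two-sided 5%. The calculation concerns sporozoites from spray catches only.

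**Formulas, under no effect of MTaT.**
- Variance that the household-level analysis keeps: V_w = p(1 − p)(1/N_c + 1/N_i)
- Between-cluster variance that it omits: V_b = (k·p)²(1/10 + 1/10)
- Design effect: DEFF = 1 + V_b/V_w
- True type I error: 2[1 − Φ(1.96/√DEFF)]

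**Numbers.** N_c = 120 × 24 = 2880 and N_i = 60 × 24 = 1440. V_w = 0.03 × 0.97 × (1/2880 + 1/1440) = 3.03 × 10⁻⁵.

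| Scenario | k | V_b | DEFF | True type I error |
|---|---|---|---|---|
| Base case | 0.25 | 1.125 × 10⁻⁵ | 1.37 | 9.4% |
| Base case | 0.3 | 1.62 × 10⁻⁵ | 1.53 | 11.4% |
| Half of variation shared within facility (V_b halved) | 0.25 | 0.5625 × 10⁻⁵ | 1.19 | 7.2% |
| Half of variation shared within facility (V_b halved) | 0.3 | 0.81 × 10⁻⁵ | 1.27 | 8.2% |
| Low cluster variation | 0.1 | 0.18 × 10⁻⁵ | 1.06 | 5.7% |

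**Sensitivity to the assumed rate and yield.** Over p = 1% to 5% and 0.5 to 2 mosquitoes per house at 24 months, the formula runs from 5.7% (p = 1%, 0.5 per house, k = 0.25) to 24% (p = 5%, 2 per house, k = 0.3). With k = 0.1 it stays between 5.1% and 7.4%.

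**Simulation check.** 2000 replicates per scenario, with gamma cluster and house effects, so that mosquitoes from one house are correlated.
- The household-level sandwich test rejected in 8.8% (base case, k = 0.25), 11.2% (base case, k = 0.3), 8.4% (k = 0.3, half shared), 4.1% (lowest scenario) and 22.8% (highest scenario).
- A sandwich test with the cluster as subject but no small-sample correction rejected in 6.4% to 8.8%.
- A t-test on the ten within-facility differences in cluster rates rejected in 4.4% to 5.7%.

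**Core area.** Study design limits the sampling frame for evaluations to the core, and the text above Table 1 repeats this for participants' households. The Table 1 entomology row does not mention the core. Neither do the cross-sectional and cohort rows, although both of those evaluations are core-limited in their own sections or in Table 2.

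**The case against.** The strongest objections concern size, and most of them stand.

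- **Merged controls.** Each merged control cluster consists of two separately allocated clusters. If its 12 houses are spread over both, the between-cluster term becomes 1/10 + 1/20 and the base case falls from 9.4% and 11.4% to 8.3% and 9.8%. With half of the variation also shared within facilities, it is 6.6% and 7.4%.
- **Allocation within facility.** The clusters abut and were placed around the same facility to limit spatial differences in transmission. Variation common to one facility largely cancels between arms. If all of it were common, there would be no inflation.
- **Borrowed CV.** The 0.3 is a human-prevalence figure, described as conservative and covering both cluster and compound variance.
- **Larger catches.** Assuming 3 to 5 mosquitoes per house, a reader might infer error rates of 22% to 30%. That calculation treats mosquitoes from one house as independent, which is the correlation the household GEE does handle. Those figures are upper bounds and should not be the headline.
- **Oocysts.** Oocyst detection needs mosquitoes held alive, and these come from the non-random live collections with no fixed number of houses. The arithmetic does not carry over to oocysts. The error in the unit of correlation does.

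Two further readings are tempting but unsupported. One is that household grouping captures almost nothing because houses are drawn without replacement: the article does not say whether this applies across months, and several mosquitoes from one house are correlated even if it is never revisited. The other is that buffer houses were sampled and added mosquito mixing: the article does not show this, and such contamination would be expected to pull the effect toward the null.

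An unseen analysis plan may nest households within clusters. The article, however, does not leave the level open. It names one, and that level lies below the unit of allocation.

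**Conclusion.** The model is wrong as written for a listed primary objective. The direction is certain whenever clusters around one facility differ in mosquito infection rate. The size is uncertain and probably moderate: a true error of about 7% to 11% is a fair mid-range under the assumptions shown, close to the nominal level if clusters within a facility hardly differ, and higher if catches or infection rates are larger.

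A reader might infer that the trial's one primary test is invalid. The article does not support that. It lists several primary objectives, and Data analysis reserves the term primary outcome for microscopically confirmed parasitaemia in the cohort and surveys. The fault concerns the entomological comparisons. The core-area wording is an ambiguity to clarify.

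**What to change.** Make the randomised cluster the GEE subject. Households are nested in clusters, so their correlation is then covered as well. Include health facility as a stratum and use a small-sample correction to the sandwich variance, which the simulation shows is needed with 20 clusters. Alternatively, compare cluster-level rates within facility with a paired t-test. State whether the merged control area counts as one cluster or two, and apply the same unit to oocysts from the live collections.

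Reword the Table 1 entomology row to agree with the core-area rule, or state that entomology is an exception.

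The cost is one model statement, a re-run and one table cell. No new data are needed. Intervals will widen if clusters differ. If it turns out that buffer houses were sampled, restricting to core houses would lose some mosquitoes.
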